### 3.2.4 Criteria for Stopping Treatment

(1) Disease progression;

(2) Unbearable toxicity after dose reductions;

(3) Patient refusal;

(4) Investigator decision that stopping treatment was in the best interest of the patient;

(5) Death.

## 3.3 Research Design

### 3.3.1 Technical Route

[figure not shown]

[figure not shown]

### 3.3.2 Drug Administration

- Oxaliplatin, 130 mg/m^2 intravenously on day 1;
- Apatinib, 500 mg orally once daily on days 1 to 21;
- S-1 (Tigio), 40-60 mg orally twice daily on days 1 to 14.

The dose of S-1 is based on body surface area (BSE):

| BSE                                    | Dose     |
|----------------------------------------|----------|
| < 1.25m                    | 40mg Bid |
| 1.25m  - 1.5m  | 50mg Bid |
| > 1.5m                     | 60mg Bid |

### 3.4 Research Flow

Start Date: The date on which the written informed consent is signed

End Date: The last day of the post-treatment period (eg, 30 days after the last drug administration).

The expected treatment duration of this study is 36 months, including 24-month enrollment period. Each participants will be followed up from the Start Date to the End Date, and then for at least 5 years.

If some participant receives a new anti-cancer therapy, monitoring of AEs will be terminated at the beginning of this therapy.

### **3.5 Assessment of Efficacy and Safety**

#### **3.5.1 Efficacy Assessment**

- Primary Outcome Measures

R0 resection rate

- Secondary Outcome Measures

Pathological response rate: major pathological response rate (G2b+G3, see Appendix 1);

Radiologic response rate: complete response (CR) + partial response (PR), according to RECIST 1.1;

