### **3.2 Criteria for Study Population**

#### **3.2.1 Inclusion criteria**

- (1) Age from 18 to 75 years
- (2) Primary gastric adenocarcinoma (papillary, tubular, mucinous, signet ring cell, or poorly differentiated) confirmed pathologically by endoscopic biopsy
- (3) cT2-4/N+M0 at preoperative evaluation according to the American Joint Committee on Cancer (AJCC) Cancer Staging Manual Seventh Edition
- (4) No distant metastasis is observed. And the spleen, pancreas or other adjacent organs are not involved by the tumor.
- (5) Performance status of 0 to 2 on Eastern Cooperative Oncology Group scale (ECOG)

(6) Without previous surgical, chemotherapy, radiotherapy, immunotherapy, or targeted therapy for gastric cancer.

(7) Estimate life is equal or more than 3 months

(8) No serious heart, lung, liver dysfunction; no jaundice or obstruction of the digestive tract; no acute infection

(9) The main organ function is normal, and meet the following criteria:

blood routine examination (No blood transfusion within 14 days)

HB $\geq$ 100g/L,

WBC $\geq$ 3.5 $\times$ 10^9/L,

ANC $\geq$ 1.5 $\times$ 10^9/L,

PLT $\geq$ 100 $\times$ 10^9/L;

blood biochemical examination

BIL $<$ 1.5 Upper Limit Of Normal (ULN) ,

ALT and AST $<$ 2.5ULN, GGT $\leq$ 1.5 $\times$ ULT;

Cr $\leq$ 1ULN, creatinine clearance  $>$  60ml/min (Cockcroft-Gault formula)

(10) Written informed consent

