## **6.2 Definitions of Analysis Sets**

Full Analysis Set (FAS): included patients who receive at least one cycle of neoadjuvant treatment.

Per-protocol Set (PPS): included patients who comply with the study protocol, have good compliance, do not take prohibited drugs during the treatment, receive surgery, and complete the CRF. Analysis of the efficacy should be performed in both FAS and PPS populations.

Safety Analysis Set (SAS): included patients who receive at least one cycle of neoadjuvant treatment and have safety records.

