#### **- Secondary Efficacy Measures**

Calculate the pathological/radiologic response rate with 95% CI. The Kaplan-Meier method is used to analyze overall survival (OS) and disease-free survival (DSS), and the differences are assessed with log-rank tests.

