## **Appendix 3**

### **Response Evaluation Criteria in Solid Tumors (RECIST) Version 1.1**

#### **Response criteria**

This section provides the definitions of the criteria used to determine objective tumour response for target lesions.

- **Evaluation of target lesions**

**Complete Response (CR):** Disappearance of all target lesions. Any pathological lymph nodes (whether target or non-target) must have reduction in short axis to <10 mm.

**Partial Response (PR):** At least a 30% decrease in the sum of diameters of target lesions, taking as reference the baseline sum diameters.

**Progressive Disease (PD):** At least a 20% increase in the sum of diameters of target lesions, taking as reference the smallest sum on study (this includes the baseline sum if that is the smallest on study). In addition to the relative increase of 20%, the sum must also demonstrate an absolute increase of at least 5 mm. (Note: the appearance of one or more new lesions is also considered progression).

**Stable Disease (SD):** Neither sufficient shrinkage to qualify for PR nor sufficient increase to qualify for PD, taking as reference the smallest sum diameters while on study.

- **Evaluation of non-target lesions**

This section provides the definitions of the criteria used to determine the tumour response for the group of non-target lesions.

While some non-target lesions may actually be measurable, they need not be measured and instead should be assessed only qualitatively at the time points specified in the protocol.

**Complete Response (CR):** Disappearance of all non-target lesions and normalisation of tumour marker level. All lymph nodes must be non-pathological in size (<10 mm short axis).

**Non-CR/Non-PD:** Persistence of one or more non-target lesion(s) and/or

645 maintenance of tumour marker level above the normal limits.

646 Progressive Disease (PD): Unequivocal progression (see comments below) of  
647 existing non-target lesions. (Note: the appearance of one or more new lesions is  
648 also considered progression).

649

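### The radiologic response rate is taken over all FAS and PPS patients, although entry requires no target lesion and Appendix 3 allows partial response only through target lesions

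*Protocol*

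**What the plan says.** **Endpoint.** Protocol section 3.5.1 lists, as a secondary measure, "Radiologic response rate: complete response (CR) + partial response (PR), according to RECIST 1.1". Under Secondary Efficacy Measures the instruction is "Calculate the pathological/radiologic response rate with 95% CI"; no denominator specific to this endpoint is named.

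**Population.** Section 6.2 (Definitions of Analysis Sets) states "Analysis of the efficacy should be performed in both FAS and PPS populations". The first set is defined as "Full Analysis Set (FAS): included patients who receive at least one cycle of neoadjuvant treatment". The PPS adds protocol compliance, surgery and a completed CRF. Neither definition mentions a target or measurable lesion.

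**Entry.** Section 3.2.1 describes extent of disease by clinical stage, "cT2-4/N+M0 at preoperative evaluation according to the American Joint Committee on Cancer (AJCC) Cancer Staging Manual Seventh Edition", and excludes distant metastasis and involvement of adjacent organs. None of its ten criteria asks for a target lesion, and the exclusions in section 3.2.2 do not bring one in.

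**Response rule.** Appendix 3 defines PR as "At least a 30% decrease in the sum of diameters of target lesions, taking as reference the baseline sum diameters". For non-target lesions, CR is "Disappearance of all non-target lesions and normalisation of tumour marker level", with all nodes non-pathological in size. The intermediate category, Non-CR/Non-PD, is "Persistence of one or more non-target lesion(s) and/or" a marker level that stays above normal. The third category is PD. There is no PR for non-target lesions.

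**The concern.** Each provision is reasonable alone; the difficulty comes from applying them together. A patient whose disease is entirely non-target has no baseline sum of diameters, so PR cannot be assigned. Shrinkage short of complete disappearance is recorded as Non-CR/Non-PD, which the endpoint does not count. The patient nevertheless stays in the denominator.

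The reported rate then depends on two things: how often tumours respond, and how many patients had disease in which PR could be scored. In a single-arm trial no concurrent group shares the second component, so a reader who sets the rate beside an outside figure cannot separate the two.

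**Working it through.** The protocol gives no response rate, null value, target or expected share of patients with target lesions, so there is no stated figure to reproduce. The check is of the text first, then of the possible size.

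**Step 1: which categories count as response under Appendix 3.**

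| Disease at baseline | Possible categories | Counted as response (3.5.1) |
|---|---|---|
| At least one target lesion | CR, PR, SD, PD | CR, PR |
| Non-target lesions only | CR, Non-CR/Non-PD, PD | CR only |

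Both rows can pass sections 3.2.1 and 3.2.2, and both fall within the FAS and, with compliance and surgery, the PPS.

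**Step 2: formula.** Let *f* be the share of the set without a target lesion, *p* the CR+PR rate among those with one, and *c* the CR rate among those without.

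- Rate over the whole set = (1 − *f*) × *p* + *f* × *c*
- Shortfall against *p* = *f* × (*p* − *c*)

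The shortfall is zero if *f* = 0 or *c* = *p*. It is largest at *c* = 0, where the whole-set rate is at its lowest, (1 − *f*) × *p*.

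**Step 3: inputs.** The planned sample size is 50 (synopsis); for illustration all 50 are taken to be in the FAS. The values of *f*, *p* and *c* are assumptions.

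**Step 4: lowest case, *c* = 0, exact (Clopper-Pearson) 95% CI.**

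| Assumed *f* | Assumed *p* | Rate in all 50 | Rate in patients with a target lesion |
|---|---|---|---|
| 10% | 60% | 27/50 = 54.0% (39.3–68.2) | 27/45 = 60.0% (44.3–74.3) |
| 20% | 70% | 28/50 = 56.0% (41.3–70.0) | 28/40 = 70.0% (53.5–83.4) |
| 40% | 80% | 24/50 = 48.0% (33.7–62.6) | 24/30 = 80.0% (61.4–92.3) |

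Over *f* from 10% to 40% and *p* from 50% to 80%, the shortfall *f* × *p* runs from 0.10 × 0.50 = 5 points to 0.40 × 0.80 = 32 points.

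**Step 5: allowing non-target CR.** With *f* = 40%, *p* = 60% and *c* = 30%, the whole-set rate is 0.60 × 0.60 + 0.40 × 0.30 = 0.36 + 0.12 = 48%. With *c* = 0 it would be 36%. The shortfall against 60% is therefore 12 points, not 24. Multiplying *p* by the share with a target lesion gives only the lower end.

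**The case against.** **The affected group may be empty.** No provision says that any enrolled patient will lack a target lesion. Appendix 3 as reproduced gives no rule for choosing target lesions, and the stage criterion can be read as requiring clinically positive nodes, which would make such patients less likely. This stands as a limit on size. It does not remove the point, because nothing in the entry criteria guarantees a target lesion.

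**An evaluable subset is usually left to the SAP.** In general that is so. Here, however, the protocol names the sets for efficacy and conditions neither on a target lesion. That wording does not forbid a further analysis, which is why the remedy is an addition and not the correction of a contradiction.

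**A rate over all treated patients is a legitimate conservative summary.** This also stands. A reader might infer that the FAS rate is wrong or simply biased downward. The documents do not support that: the protocol never states that its target is response among patients with measurable disease, and the FAS rate is low only relative to that quantity. Nor should the FAS rate be replaced, since patients with non-target CR are responders under section 3.5.1 and would drop out of the result.

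**Tempting extensions.** A reader might infer that patients without a target lesion can never respond; Appendix 3 gives them CR. A reader might also expect sites to measure unsuitable lesions to create a target, adding noise to response and progression calls. Nothing in the protocol indicates this, and Appendix 3 lets progression be called from non-target or new lesions as well.

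**Conclusion.** The point holds in limited form. As written, any patient with non-target disease only enters the FAS and PPS denominators with CR as the sole route to response, so the reported rate may understate response among patients in whom PR can be assessed. How far is unknown: the shortfall is nil if every patient has a target lesion and at most *f* × *p* otherwise. The 14-point gap between 56% and 70% rests on assumed values of 20% without a target lesion, 70% response among the rest and no non-target CR; any such CR narrows it.

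This is a minor point. The endpoint is secondary and descriptive, the protocol attaches no threshold or decision to it, and the primary R0 resection rate is untouched.

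**What to change.** In section 3.5.1 and in section 6.2 (analysis sets and Secondary Efficacy Measures):

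1. Keep the CR+PR rates in the FAS and PPS.
2. Add the CR+PR rate with 95% CI among FAS and PPS patients who have at least one target lesion recorded on the screening scan before cycle 1. Count those with no later scan as non-responders.
3. Report the number without a target lesion and their best category (CR, Non-CR/Non-PD, PD) separately.

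Recording target lesions before treatment stops the subset from being chosen after response is known. Eligibility need not change. No procedure is added, since imaging is already required at screening (section 4.1) and after every two neoadjuvant cycles (section 4.2). The cost is some wording, the recording of target lesions at baseline, and a smaller denominator with a generally wider interval for the added rate. In the 20%/70% illustration the interval is 53.5–83.4 (29.9 points wide) on 40 patients, against 41.3–70.0 (28.7 points) on 50.

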#### **3.5.2 Safety Assessment**

(1) Surgical safety: including surgical mortality, surgical morbidity (bleeding, anastomotic leakage, wound infection), reoperation rate, length of stay, etc.

(2) Drug safety: including AEs, SAEs, and drug-related AEs (e.g. hypertension, hand-foot syndrome, and proteinuria).

### **3.6 Distribution, Storage and Management of Drugs**

Drug distribution must be strict. Special persons from each centers are responsible for distributing and keeping drugs. Researchers should fill in the Registration Forms for Drugs at each visit.

According to the requirements of GCP, study drugs should be uniformly stored, distributed and recycled by research centers. The drugs should be stored at a sealed, protected from light, and room temperature environment. The validity period is tentatively set for 2 years.

## **4. Study Procedure**

### **4.1 Screening Period**

The following screening steps should be completed within 2 weeks before starting treatment:

- Demographics characters: gender, date of birth, ethnicity, height, weight, etc.
- Diagnosis of tumors: date of diagnosis, histological classification, clinical stage, etc.
- History of comorbidity: such as history of diabetes, hypertension or chronic

obstructive pulmonary disease.

- Imaging examination: including whole abdominal computed tomography (CT) or magnetic resonance imaging (MRI), and chest X-ray. Other means of evaluation: gastrointestinal radiography, ultrasonography of other organs, and positron emission tomography (PET)-CT.

After admitting, patients meeting the selection criteria should be screened out. For these patients, researchers will introduce this trial in detail, and the ICF will be signed if the patients agree to participate.

The following screening steps should be completed within 1 weeks before starting treatment:

- ECOG PS score;
- Vital signs: heart rate, breathing rate, temperature, and blood pressure;
- Physical examination: Head and face, skin system, lymph nodes, eyes, ear, nose, throat, mouth, respiratory system, cardiovascular system, abdomen, genitourinary system, musculoskeletal, nervous system, and mental status.
- Peripheral blood routine: Hb, RBC, WBC, ANC, and PLT.
- Urinary routine: Urine protein and occult blood tests; if the semi-quantitative method shows protein  $\geq 2+$  (eg, urine test strips), a 24-hour urinary protein quantification test should be performed. The 24-hour urinary protein quantification of enrolled patients must be  $<1\text{g}$ .
- Stool routine: Occult blood tests;
- Blood chemistry: Total bilirubin, ALT, AST, AKP, r-GT, TP, ALB, BUN, and CA.
- Coagulation tests : PT, APTT, TT, and Fbg;
- Electrocardiograms: 12-lead electrocardiograms;
- Pregnancy tests (for women at childbearing age).

#### **4.2 Neoadjuvant Treatment Period**

Intervention group: All enrolled patients receive 2-5 preoperative cycles of apatinib (500 mg orally once daily on days 1 to 21 and discontinued in the last cycle) plus SOX (S-1, 40-60 mg orally twice daily on days 1 to 14; oxaliplatin, 130 mg/m^2 intravenously on day 1) every 3 weeks.

- During neoadjuvant treatment, physical examination, ECOG PS assessment, tumor markers, and electrocardiograms are performed on day

1 of cycles 2, 3, 4, and 5. If cardiac pains or palpitations occur, myocardial enzyme spectrum (creatin kinase, lactate dehydrogenase), electrocardiogram, and cardiac ultrasound should be immediately performed;

- Peripheral blood routine and blood chemistry are performed on day 7 of cycle 1 and days 1, 7 of cycles 2, 3, 4, and 5;
- Urinary routine, stool routine, and coagulation tests are performed on day 1 of cycles 2, 3, 4, and 5;
- Imaging examination should be performed under the same conditions (layer thickness of scanning, use of contrast agent, etc.) as possible. The lesions detected at the baseline should be followed up every 2 cycles;
- Discomforts during the treatment should be recorded and graded according to the the NCI-CTCAE, version 4.0. If necessary, develop the treatment plan with the department of oncology, and record the reasons for dose adjustment or delay, supportive treatment, and outcomes in the CRF;
- Blood pressure monitoring is performed by the patient himself/herself and recorded in a diary card. Measurement should be done at least 3 times a week during the first 2 cycles. If abnormal, the blood pressure should be monitored daily; otherwise the blood pressure is measured weekly after 2 cycles. At each visit, researchers should measure the blood pressure again. Before measurement, smoking and coffee are not permitted. Take a sitting position. The elbows should be placed at the same level as the heart, and each measurement should be taken on the same side.

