### 3.2.3 Rejection criteria

(1) Do not meet the inclusion criteria and meets the exclusion criteria;

(2) Simultaneous application of CFDA-approved modern Chinese medicine or immunomodulators for the treatment of gastric cancer;

(3) Radiation therapy or other local treatments during the study periods;

(4) Incomplete data;

(5) Do not take medicine according to the dosage, method, and treatment prescribed in the protocol.

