#### **4.3 Preoperative evaluation and surgical period**

After completing neoadjuvant treatment, peripheral blood routine, blood biochemistry, stool routine, urine routine, 12-lead electrocardiograms, tumor markers, and coagulation function should be performed to evaluate the efficacy as well as the patients' physical condition. Without clear surgical contraindications and with the patients' consent, surgery will be performed 2–4 weeks later. If disease progresses, radiochemotherapy or salvage surgery is recommended.

- Record the results of peripheral blood routine, blood biochemistry, stool routine, urine routine, 12-lead electrocardiograms, tumor markers, and coagulation tests which are performed 7 days before and after the surgery;

- Retain pathological tissue specimens after surgery;
- Record the reasons for not surgery;
- Record operation time, blood loss, and intraoperative complications (e.g. major bleeding);
- Record postoperative complications and management;
- Record pathological type, number of lymph nodes harvested and metastasis;
- Record postoperative hospital days.

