#### 4.4 Adjuvant treatment period

Intervention group: All enrolled patients receive 6 postoperative cycles of apatinib (500 mg orally once daily on days 1 to 21) plus SOX (S-1, 40-60 mg orally twice daily on days 1 to 14; oxaliplatin, 130 mg/m^2 intravenously on day 1) every 3 weeks.

- During adjuvant treatment, peripheral blood routine and blood chemistry are performed on days 1, 7 of cycle 1 and day 1 of cycles 2, 3, 4, 5, and 6;
- Physical examination, ECOG PS assessment, tumor markers, and electrocardiograms are performed on day 1 of each cycle;
- Imaging examination should be performed under the same conditions (layer thickness of scanning, use of contrast agent, etc.) every 3 cycles;
- Discomforts during the treatment should be recorded and graded according to the NCI-CTCAE, version 4.0. If necessary, develop the treatment plan with the department of oncology, and record the reasons for dose adjustment or delay, supportive treatment, and outcomes in the CRF;
- Blood pressure monitoring is performed by the patient himself/herself and recorded in the diary card. Measurement should be done at least 3 times a week during the first 2 cycles. If abnormal, the blood pressure should be monitored daily; otherwise the blood pressure is measured weekly after 2 cycles. At each visit, researchers will measure the blood pressure again. Before measurement, smoking and coffee are not permitted. Take a sitting position. The elbows should be placed at the same level as the heart, and each measurement should be taken on the same side.

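### Section 4.2 stops apatinib in the last preoperative cycle, but the synopsis and 3.3.2 omit this exception and 4.2 does not define its extent

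*Protocol*

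**What the plan says.** Three places in the protocol describe apatinib dosing that applies before surgery.

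- The Intervention row of the synopsis and section 3.3.2 carry the same line: "Apatinib, 500 mg orally once daily on days 1 to 21". Neither gives a number of cycles, separates preoperative from postoperative treatment, or refers to section 4.2.
- Section 4.2 sets the preoperative course. It opens with "All enrolled patients receive 2-5 preoperative cycles of apatinib" and gives the schedule as "500 mg orally once daily on days 1 to 21 and discontinued in the last cycle", combined with SOX every 3 weeks.

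Three other places bear on the point.

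- Section 4.4 sets the postoperative course without any last-cycle exception: "All enrolled patients receive 6 postoperative cycles of apatinib (500 mg orally once daily on days 1 to 21".
- Section 4.3 says that, once neoadjuvant treatment is complete, "surgery will be performed 2–4 weeks later". It does not define the day of completion and states no separate apatinib-free interval.
- Rejection criterion (5) in section 3.2.3 reads "Do not take medicine according to the dosage, method, and treatment prescribed in the protocol". The per-protocol set (PPS) is defined as "included patients who comply with the study protocol, have good compliance", with further conditions.

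**The concern.** The last-cycle exception appears once in the readable text and is missing from the two general dosing statements. A site working from the synopsis or 3.3.2 would give apatinib through day 21 of the last cycle before surgery. A site working from 4.2 would not.

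Section 4.2 is also unclear on its own terms. The exception can mean no apatinib at all in the last cycle, or a stop at some unstated day within it. The same sentence counts that cycle among the preoperative cycles of apatinib plus SOX, which does not help to choose between the two. If the whole cycle is meant, the site must know on day 1 that the cycle is the last, and with 2 to 5 cycles allowed the text does not say how that is decided. Two sites that both follow 4.2 in good faith can therefore treat differently.

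Two things are at stake. In a single-arm study of this combination, preoperative exposure is part of the intervention to which the R0 resection and response rates are attributed. The interval from last apatinib dose to operation is relevant to surgical safety outcomes that the protocol names: bleeding, anastomotic leakage and wound infection. A lesser consequence is that compliance with the protocol cannot be judged uniformly while the prescribed last-cycle dosing is open.

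**Working it through.** The protocol states no figure for exposure or drug-free interval, so there is none to reproduce. The check is arithmetic on the stated schedule.

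**Inputs**

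- Cycle length 21 days, 2 to 5 preoperative cycles, S-1 on days 1 to 14 (section 4.2).
- Apatinib on days 1 to 21 (synopsis, 3.3.2, 4.2), with the last-cycle exception (4.2 only).
- Surgery 2-4 weeks, that is 14-28 days, after completion (4.3).
- Assumption, because 4.3 leaves it open: completion is either day 21 of the last cycle or the last study dose taken.

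**Exposure.** Let c be the number of preoperative cycles and d the last day of the final cycle on which apatinib is taken. Full dosing is d = 21 and whole-cycle omission is d = 0.

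Apatinib days = 21 × (c − 1) + d. The shortfall against full dosing is 21 − d.

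| Cycles | General line applied to all preoperative cycles (d = 21) | Whole last cycle omitted (d = 0) | Largest reduction |
|---|---|---|---|
| 2 | 42 | 21 | 21/42 = 50% |
| 3 | 63 | 42 | 21/63 = 33.3% |
| 4 | 84 | 63 | 21/84 = 25% |
| 5 | 105 | 84 | 21/105 = 20% |

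A partway stop lies between the columns. For example, d = 7 gives a shortfall of 14 days and d = 14 gives 7 days. The range is 0 to 21 days per patient.

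**Apatinib-free interval before surgery.** Interval = (completion day + 14 to 28) − d, counting days from the start of the last cycle. With whole-cycle omission, the last apatinib dose falls on the final day of the preceding cycle, which is day 0 on this count.

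- Full dosing, completion on day 21: surgery on days 35-49, and 35 − 21 to 49 − 21 = 14-28 days.
- Whole cycle omitted, completion on day 21: 35 − 0 to 49 − 0 = 35-49 days. The gap is 21 days.
- Whole cycle omitted, completion at the last dose taken (S-1 on day 14): surgery on days 28-42, and the interval is 28-42 days. Under the same definition, full dosing completes on day 21 and stays at 14-28 days. The gap is 14 days.

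If completion were fixed at day 14 even with full apatinib dosing, the figures would be 28 − 21 to 42 − 21 = 7-21 days against 28-42 days, again a gap of 21 days.

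A partway stop narrows each gap. With d = 7, the interval is 28-42 days if completion is day 21, and 21-35 days if completion is S-1 on day 14.

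**The case against.** The strongest reply is that there is no contradiction. The synopsis and 3.3.2 list days within a cycle. They do not say that the line holds in each cycle, and it also has to cover the six postoperative cycles of 4.4, where no exception applies. Section 4.2 repeats days 1 to 21 and adds a qualifier for one period, as a specific rule does to a general one. No site could treat from 3.3.2 alone, because the number of cycles and the three-week interval appear only in 4.2 and 4.4. A site that reads the number of preoperative cycles reads the exception in the same sentence. The technical-route figures in 3.3.1 are not shown and may carry the rule.

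Most of this stands. A reader might infer that the protocol prescribes two explicit and incompatible schedules. The documents do not support that. What the reply leaves untouched is the ambiguity inside 4.2: giving it priority does not tell a site on which day apatinib ends, or how the last cycle is known beforehand. No text says which section prevails, either.

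A reader might also infer that patients treated under one passage will be rejected under 3.2.3(5) and lost from the analysis. That goes too far. A patient treated under 4.2 has followed an explicit instruction. Efficacy is analysed in the full analysis set (FAS) as well as the PPS, and the FAS requires only one cycle of neoadjuvant treatment. The FAS estimate of the R0 rate loses no patient through this wording.

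**Conclusion.** The point holds as an exception that is missing from two of the three dosing statements and undefined in extent in the third. It leaves preoperative apatinib open by 0 to 21 days per patient, which at the extreme halves exposure in a two-cycle patient and lowers it by a fifth in a five-cycle patient. The apatinib-free interval before surgery is open by up to 21 days if completion is a fixed day of the last cycle, or up to 14 days if completion is the last dose taken.

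The upper ends assume that the whole last cycle is omitted and that dosing is otherwise at the nominal schedule without interruptions. The interval also rests on the completion day, which 4.3 does not define. The main consequence is for the consistency of the intervention and the reading of the surgical safety outcomes. The effect on rejection criterion (5) and PPS membership is secondary. It should be corrected, and nothing here says which schedule is clinically right.

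**What to change.** Reconcile the synopsis, section 3.3.2 and section 4.2 into a single statement of apatinib dosing in the last preoperative cycle, and bring the technical-route figure into line if it differs. The statement should say:

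- whether apatinib is given, omitted for the whole cycle, or stopped on a named day;
- how and when the last of the 2 to 5 cycles is identified;
- which day counts as completion of neoadjuvant treatment for the surgical window in 4.3.

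Then judge rejection criterion 3.2.3(5) and PPS compliance against that one statement. The choice of schedule belongs to the investigators. The cost is protocol wording only, with no change to sample size, endpoints or analysis.
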